### Recruitment and Sampling

A list of patients with T1D, aged 12 to 18 years, who (1) use CGM, (2) received care in the U-M Pediatric Diabetes Clinic in the past 12 months, and (3) have at least 1 HbA_1c_ laboratory result from the past 12 months will be generated using DataDirect (University of Michigan Medical School) and Electronic Medical Record Search Engine (EMERSE) [40]—university-developed tools for performing systematic searches of structured and unstructured patient medical records [41]. The list will include basic demographic, clinical, and contact information for identified patients.

Consistent with a grounded theory approach, we will use theoretical sampling to help ensure that adequate data are collected to address our research aims. For our initial sampling strategy (a priori) [42], we seek to enroll participants with diverse diabetes outcomes and experiences. We will intentionally recruit and enroll participants with HbA_1c_ of 9% or less and more than 9% to ensure adolescents with low and high glycemic levels are represented. We aim to recruit and enroll approximately equal groups with high and low glycemic levels. A purposive sampling approach will also be leveraged using demographic and clinical factors including age, gender, years since diagnosis, and other social determinants of health (eg, family income and food insecurity measures) to create a sample with varied experiences and backgrounds. Sociodemographic backgrounds that are under-represented within the clinical population (ie, Hispanic or Latino) in the sample will be intentionally oversampled. As data collection and analysis proceed, recruitment and sampling strategies may shift to explore variation in participant responses, develop relationships between codes and categories, and add details to the descriptions and characteristics of categories in the analysis [42].

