Recruitment will be conducted in waves to allow for flexibility and needed changes to meet theoretical sampling goals. During each wave, approximately 100 to 200 identified patients will be contacted via electronic and/or postal mail up to 5 times with study information and a link to an online screening survey to confirm interest and eligibility. Study information will also be shared through (1) flyers and patient newsletters posted by the U-M Pediatric Diabetes Clinic, (2) UMHealthResearch.org, a secure platform at U-M for sharing study information with potential participants, and (3) emails and newsletters shared with patient diabetes councils. If recruitment goals are not reached through these methods, patients may also be approached in person at the U-M Pediatric Diabetes Clinic by nonclinician members of the study team.

Study eligibility criteria include: (1) current patient at Michigan Medicine with at least 1 visit and HbA_1c_ measurement in the last 6 months, (2) aged 12 to 18 years upon enrollment, (3) diagnosed with T1D for at least 6 months, (4) used CGM for at least 6 months, (5) used CGM for at least 20 days per month, (6) able to communicate in English, and (7) have access to a phone with SMS text messaging capabilities. Eligibility will be assessed via the screening survey and confirmed via medical record review.

A sample size estimate (N=30‐40) was determined a priori based on estimates of the amount of qualitative data needed to reach data sufficiency across participants with varied glycemic levels and diabetes experiences [43,44]. Due to the longitudinal nature of data collection and multiple data sources in this study, we anticipate having sufficient data to inform our grounded theory. As is common in qualitative research and grounded theory, additional data may be collected as needed to further develop findings and reach theoretical saturation [45]. The same sample will be used for quantitative data collection, including baseline surveys of diabetes characteristics and psychosocial measures, and 30 days of CGM data. Using identical samples in a convergent mixed methods design reduces threats to validity (eg, sample size legitimation) and ensures that appropriate conclusions can be drawn through integration [46,47].

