### Baseline Survey

Study participants will complete a one-time baseline survey. Measures were selected to align with components of the COM-B model and the literature on psychosocial influences on self-management and diabetes device use. The survey includes measures of diabetes self-management behaviors, depression, diabetes distress, attitudes towards diabetes technology, problem-solving, and self-efficacy with diabetes self-management. A summary of survey instruments, sample items, and their alignment with the COM-B model is included in Table 1. Additional details can be found in Multimedia Appendix 2.

**Table 1. T1:** Alignment of capability, opportunities, and motivation of behavior (COM-B) model with select data collection measures.

COM-B construct	Baseline survey items	Daily and end-of-day survey items	Semistructured interview questions
Capability (physically and psychologically able, including knowledge, decision-making, and skills)	Self-efficacy for T1D^a^ management: “[Can you…] adjust your insulin or food accurately based on how much exercise you get.” [50]. CGM^b^ self-efficacy: “I am sure I can... adjust insulin dose based on real-time data” [51].	Did you look at information from your diabetes devices in the last few hours? If no, why not?	What do you consider to be a high blood sugar? Why is this number significant to you?
Opportunity (social and environmental conditions, including social support and structural factors)	Clinical characteristics: For how long have you used CGM? How many days in the last month did you wear a CGM sensor or use CGM?	What problems, if any, did you encounter today? Were your diabetes devices useful to you today? How?	What support do you get from your health care providers that help you to use your technology?

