To test for mean differences in psychosocial and behavioral characteristics between glycemic level groups (HbA_1c_>9% and those with HbA_1c_≤9%) at baseline, 1-tailed *t* tests will be used. If the data are nonparametric, appropriate alternative tests (ie, the Wilcoxon rank paired test) will be performed. For all participants with at least 28 days of continuous glucose data, we will use linear mixed models to identify risk factors that influence blood glucose levels, model changes in blood glucose over time, and test any intervention effect resulting from longitudinal data collection. Additional statistical tests may be performed as appropriate based on the data collected. Statistical analysis will be performed on the data of all included study participants, and a statistical significance level of 5% (α=.05) will be used to test for differences and associations.

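### The fallback test for comparing the two HbA1c groups is a paired Wilcoxon test, but the groups are different adolescents and nothing pairs them

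*Protocol article*

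**What the plan says.** All the test wording is in the protocol article, under Quantitative Analysis. The purpose is given as "To test for mean differences in psychosocial and behavioral characteristics between glycemic level groups", the groups being HbA1c above 9% and HbA1c of 9% or less. The first-line method is stated as "at baseline, 1-tailed *t* tests will be used". The fallback follows: "If the data are nonparametric, appropriate alternative tests (ie, the Wilcoxon rank paired test) will be performed". The section sets the threshold too: "a statistical significance level of 5% (α=.05) will be used to test for differences and associations".

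Three statements elsewhere fix the structure of the data:

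- **Baseline Survey:** "Study participants will complete a one-time baseline survey".
- **Recruitment and Sampling, group sizes:** "We aim to recruit and enroll approximately equal groups with high and low glycemic levels".
- **Recruitment and Sampling, total size:** "A sample size estimate (N=30‐40) was determined a priori based on estimates of the amount of qualitative data needed to reach data sufficiency".

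No section describes matching an adolescent in one HbA1c group to an adolescent in the other.

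**The concern.** A paired Wilcoxon (signed-rank) test works on within-pair differences. It needs two linked values per unit, either from the same person or from deliberately matched people. The planned comparison sets one set of adolescents against another and has no such link. The fallback is introduced by *ie*, which identifies the test meant, and not by *eg*, which would offer one example among several.

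This is the only nonparametric test the article names for the between-group comparison. The Results section states directional expectations for this same contrast: lower problem-solving, self-management and device use, and higher distress and depression, in the group above 9%. Some of the scales are short (depression is measured with a two-item screen) and groups would be about 15 to 20 each, so it is plausible that the fallback will be needed. The article gives no rule for when it applies, so how often it would be used is unknown.

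**Working it through.** The article gives no power, effect size or standard deviation for this comparison, so there is no stated figure to reproduce. The check is one of design, followed by simulation of what happens if the sentence is followed.

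**1. Is there any pair?**

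- *Same person in both groups?* No. The groups are defined by one HbA1c cut-off, so each adolescent is in exactly one.
- *Two measurements per person?* No. The compared variables come from a survey completed once.
- *Matched individuals?* No. Recruitment is purposive and by HbA1c level; no individual matching is described.

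**2. Can the test be computed?** Only with equal group sizes and complete scores. The plan aims for approximately equal groups in a total of 30 to 40. Of the 11 possible totals in that range, 5 are odd (31, 33, 35, 37, 39) and cannot split equally. A paired Wilcoxon routine given 20 and 15 values stopped with an error.

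**3. If sizes are equal, does the answer depend on the pairing?** Assumptions: 18 per group, normal data, true shift 0.7 SD, 300 simulated datasets, 200 random pairings of each.

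| | Original run | Repeat, two-sided | Repeat, one-sided |
|---|---|---|---|
| Datasets where pairings disagreed at 5% | 59% | 58% | 60% |
| Datasets with 5% to 95% of pairings significant | 40% | 41% | 38% |

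As an illustration, one dataset of 18 and 18 was chosen because its one-sided rank-sum p was borderline (0.059). Over 2,000 random pairings the one-sided signed-rank p ran from 0.001 to 0.25, with the central 95% from 0.013 to 0.123. It fell below 0.05 in 40% of pairings.

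**4. Type I error and power.** Assumptions: normal data, one-sided alpha 0.05, 4,000 runs per setting, shift of 0 or 0.8 SD. For unequal groups, the larger group was cut to the size of the smaller to force pairs.

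| Split | Type I error, rank-sum | Type I error, signed-rank | Power, rank-sum | Power, signed-rank |
|---|---|---|---|---|
| 15:15 | 0.047 | 0.047 | 0.68 | 0.65 |
| 20:20 | 0.046 | 0.050 | 0.78 | 0.77 |
| 23:12 | 0.055 | 0.047 | 0.68 | 0.54 |
| 25:15 | 0.049 | 0.048 | 0.74 | 0.63 |

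At 23:12 forced pairing discards 23 − 12 = 11 of 35 participants (31%) and costs 0.68 − 0.54 = 0.14 in power. At 25:15 it discards 25 − 15 = 10 of 40 (25%) and costs 0.74 − 0.63 = 0.11.

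For reference, the usual unpaired two-mean formula (one-sided 5%, 0.8 SD) gives power of 0.71 at 15 per group and 0.81 at 20 per group, so the rank-sum figures are in the expected range.

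**The case against.** The strongest reply is that this is a misnamed test of limited consequence. The sentence promises alternatives that are appropriate, the section allows further tests to suit the data, and an analyst would probably run the rank-sum test anyway. With unequal groups the software would refuse, so the slip would be noticed before reporting. The study aims to build a grounded theory and assess feasibility. Neither aim turns on this p-value, and the sample size was not set for it.

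The simulations can also be read less dramatically. Under random pairing, type I error is not inflated. With equal groups, average power is almost unchanged. In a further run at 18 per group and 0.7 SD, the paired verdict agreed with the rank-sum verdict in 88% to 89% of pairings on average. The shift sizes are assumptions, and the simulated data were normal although the fallback is meant for data that are not.

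Most of this stands as a limit on the harm. None of it makes the named test fit. The general wording does not help, because the parenthesis says which test is meant; permission to add tests does not correct the one specified. Nor is this a detail left to a fuller plan, since the article positively names a test that does not apply. If an analyst quietly substitutes the rank-sum test, the published plan and the analysis disagree with no record of why.

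**Conclusion.** The concern holds. The named fallback does not apply to a comparison of two independent groups. This follows from the article's own description of the groups, the single survey and the recruitment, and needs no assumption.

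The size of the effect does rest on assumptions. At 18 per group and a 0.7 SD shift, the 5% verdict depended on row order in close to 60% of datasets. At splits of 23:12 or 25:15 and a 0.8 SD shift, forcing pairs cost 0.14 or 0.11 in power. The test is inapplicable in the sense of being undefined or arbitrary; the evidence does not show inflated false positives. The affected analysis is a fallback for a supporting comparison, so the study's main qualitative conclusions are not threatened, but the sentence should be corrected before the quantitative analysis is run.

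**What to change.** In Quantitative Analysis, replace the paired Wilcoxon test with the Wilcoxon rank-sum (Mann-Whitney) test for two independent groups. It would help, though the correction does not require it, to report the Hodges-Lehmann shift with a 95% confidence interval beside the p-value.

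The cost is one phrase. Sample size, alpha, data collection and participant burden do not change. The article describes enrollment as still under way in December 2025 and likely to continue into early 2026, so on that timetable the correction could be recorded before analysis as a documented change and not as an unexplained departure.

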**Results:**

As of December 2025, 25 participants have enrolled in this study. We expect SMS text messaging survey completion rates and CGM use near 70% throughout the study period. We anticipate findings to become available in the following several years through conference presentations and peer-reviewed publications.

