### Data Collection Procedures

Overall study participation will last approximately 6 weeks. Participants will complete (1) a one-time baseline survey to collect participant demographics, diabetes history, and psychosocial influences on T1D self-management; (2) 30 days of daily SMS text messaging surveys and CGM to evaluate real-time psychosocial influences on T1D self-management and glycemic levels; and (3) an optional semistructured interview to gain additional insights on T1D self-management approaches. Following enrollment and prior to data collection, participants will receive basic training on how to complete the daily surveys using a practice survey that includes sample questions with various formats (open-ended and closed-ended) and provides examples of survey prompts and outro messages. All survey data will be collected and managed using a secure REDCap (Research Electronic Data Capture; Vanderbilt University) database [48,49]. A study timeline and overview of data collection procedures for each participant are presented in Figure 2.

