#### Quantitative Analysis

Baseline survey metrics and clinical characteristics collected from medical records (eg, HbA_1c_) and participant response rates will be summarized using descriptive statistics. In line with the adapted STROBE (Strengthening the Reporting of Observational Studies in Epidemiology) Checklist for Reporting EMA Studies (CREMAS) from Liao et al [63], we plan to report participant attrition rates according to study days, response latency, overall and daily compliance rates (total responses per participant and average number of responses), and associations of compliance with demographic, clinical, and other time-varying variables.

In this mixed methods study, quantitative measures will be used to characterize the sample and expand understanding of each participant’s experience when integrated with qualitative findings. CGM-derived metrics of glycemic control will include those recommended by consensus guidelines from Battelino et al [64] such as sensor use time, time in ranges (ie, above and below), and the glucose management indicator. A minimum of 14 days of CGM data with sensor use 70% of the time has been previously established as sufficient for analysis. The *iglu* R package (R Foundation for Statistical Computing) [65,66] will be used to process and analyze all collected CGM data, and interpolation will be used for small windows of missing data (eg, 45 min). Additional analysis packages (eg, *Best Linear IMPutation*) will be used to impute expected longer periods of missing data (ie, periods of signal loss and sensor malfunction) to reduce bias introduction and evaluate the randomness of missing data and impute missing values, where appropriate [67].

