## Results

This study was reviewed and approved by the institutional review board in January 2025 and enrolled its first participant in April 2025. As of December 2025, 25 participants have enrolled in this study, and we anticipate meeting our enrollment goal of approximately 30 to 40 participants in early 2026. We anticipate findings to become available in the following several years through conference presentations and peer-reviewed publications. Furthermore, findings will inform the development of an intervention to address diabetes self-management and decision-making in adolescents with T1D.

Few previous applications of real-time data collection have leveraged conversational SMS text messaging (where questions are sent one-at-a-time following participant responses), and, as such, there is little data on participant burden and compliance available for this method; however, early studies using closed-ended surveys indicate high satisfaction and compliance rates (≤95%) among adolescents and young adults [74], especially when fewer prompts were used [75,76]. As a result, our study incorporated several recommendations for burden reduction and compliance optimization such as working with a population that feels connected to our study objective, using shorter, less frequent prompts, allowing a window of 2+ hours for responses, allowing the use of participants’ own devices, providing a monetary incentive after completing the study, and co-developing surveys with youth with lived experience of T1D from the T1DYAC [77,78]. As a result, we are hopeful for response rates of at least 70% in this study. Likewise, we expect themes emerging from the analysis of feasibility and acceptability responses to highlight overall participant satisfaction and low burden.

We anticipate that sensor use time will be above 75%, as this population will already use CGM prior to study enrollment. In addition, we anticipate that participants with HbA_1c_ of more than 9% will report lower problem-solving, self-management behaviors, and diabetes device use, and higher diabetes distress and depression compared with those with HbA_1c_ of 9% or less.

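### The linear mixed models keep only participants with at least 28 of 30 days of CGM data, an unexplained and undefined cut-off that can select on sensor wear and shrink a sample of 30 to 40

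*Protocol article*

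**What the plan says.** All references are to the protocol article.

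- **Model entry rule** (Quantitative Analysis): "For all participants with at least 28 days of continuous glucose data, we will use linear mixed models to identify risk factors". The same sentence gives the models two further purposes: describing change in glucose over time, and testing whether taking part in the data collection itself altered glucose.
- **Analysis population** (same paragraph): "Statistical analysis will be performed on the data of all included study participants".
- **Data sufficiency** (Quantitative Analysis, preceding paragraph, directly after the list of CGM summary metrics): "A minimum of 14 days of CGM data with sensor use 70% of the time has been previously established as sufficient for analysis". That paragraph also plans interpolation of short gaps and imputation of longer ones.
- **Observation window** (Data Collection Procedures): "30 days of daily SMS text messaging surveys and CGM to evaluate real-time psychosocial influences".
- **Entry criterion** (Recruitment and Sampling): "used CGM for at least 20 days per month".
- **Expected wear** (Abstract, Results): "We expect SMS text messaging survey completion rates and CGM use near 70% throughout the study period".
- **Expected wear** (main Results): "We anticipate that sensor use time will be above 75%, as this population will already use CGM prior to study enrollment".

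Recruitment and Sampling and Mixed Methods Integration both present the use of the same participants in the qualitative and quantitative strands as a strength of the design. The main Results section expects participants with HbA1c above 9% to report lower device use.

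**The concern.** The cut-off demands more days than the article requires at entry and, on a strict reading, more than it expects during the study. Four other parts of the plan sit poorly with it: the expected-wear figures, the imputation of longer gaps, the shared qualitative and quantitative sample, and the sentence that all included participants are analysed.

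The rule is not needed to fit the models. A linear mixed model accepts a different number of days from each person. Under missing at random, with a correctly specified model, it needs no completeness filter.

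The filter selects on sensor wear during the 30 days. Wear may be related to glucose and to the candidate risk factors, and it may itself respond to being studied, which is one of the questions put to these models. If wear is lower when HbA1c is above 9%, the filter would also thin one of the two groups that the sampling plan tries to keep about equal. At stake are biased risk-factor estimates and a small model sample drawn from only 30 to 40 people.

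**Working it through.** There is no figure in the plan to reproduce. The sample of 30 to 40 rests on qualitative data sufficiency, and no expected number for the mixed models is given.

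**Step 1. Put the thresholds on one scale (30-day window).**

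| Source | Days | Share of days |
|---|---|---|
| Mixed-model entry rule | 28 | 28/30 = 93.3% |
| Entry criterion | 20 | 20/30 = 66.7% |
| Expected wear, Abstract | 0.70 × 30 = 21 | 70% |
| Expected wear, Results (a lower bound) | 0.75 × 30 = 22.5 | 75% |

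On a strict day count, a participant at any of the last three levels falls 5.5 to 8 days short.

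**Step 2. Share of participants reaching 28 days.** Three assumptions are needed that the documents do not supply:
- wear is read as a share of days;
- each person has their own wear probability, drawn from a beta distribution with mean m and standard deviation SD;
- given that probability, days are independent.

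With s = m(1 − m)/SD² − 1, a = ms and b = (1 − m)s, the number of days is beta-binomial(30, a, b), and the share kept is P(days ≥ 28). For example, m = 0.70 and SD = 0.10 give s = 0.21/0.01 − 1 = 20, a = 14, b = 6 and P = 0.03.

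| Mean wear | SD 0.10 | SD 0.15 | SD 0.20 |
|---|---|---|---|
| 0.70 | 3% | 9% | 17% |
| 0.75 | 8% | 17% | 27% |
| 0.85 | 35% | 46% | – |
| 0.90 | 57% | 67% | – |

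Out of 40 participants this is about 1 to 11 at mean wear of 70-75% and about 14 to 27 at 85-90%. Out of 30 it is about 1 to 8 and about 10 to 20.

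**Step 3. Compare with a 14-day count.** In the same 70-75% scenarios, P(days ≥ 14) is 86-98%. This applies the day count alone and not the 70% sensor-use part of the cited standard.

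**Step 4. How far the result depends on the reading.** Sensor use is a share of time, whereas 28 days is a count. Someone with readings on all 30 days but gaps on each can have about 75% sensor use and still pass. If any reading makes a day, or days are counted after imputation, far fewer people are lost than Step 2 shows. The article does not say which applies.

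**Step 5. Plausibility of the assumed distributions.** The scenarios put 35-39% of people (mean 0.70) or 20-30% (mean 0.75) at an underlying wear below 20/30, the level required at entry. Wear in the study may fall below earlier wear, but the 70-75% rows may still be pessimistic for this population. That is why the 85-90% rows are shown.

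**The case against.** Several objections narrow the point, and they stand.

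- **Units.** Sensor use time and a day count are different measures. That 28 days means 93% wear, and that a participant behaving as expected is dropped, holds only if a day needs near-complete data.
- **The 14-day, 70% standard.** A reader might infer that the 28-day rule contradicts it. It does not, strictly: the standard follows the list of summary metrics, and a longitudinal model may have a different threshold. What remains is an unexplained departure.
- **Who is excluded.** A reader might infer that the rule removes the less engaged adolescents whom the study is about. The documents do not support this. The low engagement described in the Introduction is mainly about using device data (reviewing it, logging events, setting alerts), and enrolment is limited to regular CGM users. Lower device use above 9% HbA1c is an expectation about what participants will report, so thinning of that group is an inference.
- **All included participants.** The general sentence can be read as qualified by the specific rule shortly before it. This is a tension that needs wording, not a proven contradiction.
- **Importance.** The aims are a grounded theory and an assessment of feasibility and acceptability. The mixed models support these aims and do not carry them.
- **The alternative is not free of bias.** If gaps depend on unseen glucose, missing at random fails and including everyone does not remove all bias. Sparse contributors also say little about change over 30 days.

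None of this gives a reason for 28 days or says what a day is. Read strictly, the rule selects on wear; read loosely, it does little. Either way the sentence needs repair.

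**Conclusion.** The point holds at moderate severity. The article fixes a near-complete-data rule for the mixed models without a reason or a definition of a valid day. If a day needs near-complete data, the rule can exclude people who satisfy the entry criterion and wear the sensor as the article expects. It can then bias the risk-factor estimates through selection on wear during the study and leave few participants in the models.

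The documents do not determine the size. Under the beta-binomial assumptions and a strict day count, about 3-27% are kept at mean wear of 70-75% and 35-67% at 85-90%. The higher range matters because the Results figure is a lower bound. Under looser readings of a day, far more are kept. A near-total loss is therefore one possible outcome and not an established one.

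The qualitative, descriptive and baseline-comparison analyses are not touched, so neither study aim is threatened. Separately, the two expected-wear statements differ and should be brought into line.

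**What to change.** 1. Remove the 28-day condition. Fit the linear mixed models to every participant who shares CGM data, using the days observed.
2. Keep the 14-day, 70% standard for person-level summary metrics, and say that this is its scope.
3. Show the subset with at least 28 days as a sensitivity analysis only. Define a valid day, and state whether days are counted before or after interpolation and imputation.
4. Compare participants above and below that cut-off, by HbA1c group.
5. Give one expected-wear figure in the Abstract and the Results, stating whether it is a share of time or of days.
6. Reword the sentence on all included participants so that it agrees with the population chosen for the models.

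This is a change of wording with no new data collection, and it should be settled before the models are fitted. The price is unbalanced data, little information on change over time from sparse contributors, and reliance on missing at random, which may not hold fully if wear depends on unseen glucose. The comparison in item 4 shows how far wear differs between the HbA1c groups.

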### Demographics and Clinical Characteristics

Participant demographic information and clinical characteristics will be collected upon enrollment using an online survey. Demographic measures include age, race and ethnicity, gender, and student and/or employment status. Clinical characteristics include age at diabetes diagnosis, recent (within the last 12 mo) hospitalization for diabetes-related complications, typical medical care for diabetes, and social support for diabetes management. Finally, questions on diabetes technology use include which type and brand of CGM and insulin pump are used, for how long, and typical use (how many d in the mo and use of automated insulin delivery). The participant demographics and clinical characteristics items are included in Multimedia Appendix 1.

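### The mixed-model search for glucose risk factors is worded as confirmatory, with an uncorrected 5% per test as the only stated criterion; it should be labelled exploratory

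*Protocol article*

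**What the plan says.** All of the following is in the protocol article.

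- **Goal.** Under Quantitative Analysis, for participants with at least 28 days of continuous glucose data, "we will use linear mixed models to identify risk factors that influence blood glucose levels". The same models also serve to describe change over time and to test whether taking part altered glucose.
- **Decision rule.** The same paragraph closes with "a statistical significance level of 5% (α=.05) will be used to test for differences and associations". No adjustment, ranking of factors or primary factor is stated.
- **Open end.** "Additional statistical tests may be performed as appropriate based on the data collected".
- **Compliance.** Earlier in the section, following a reporting checklist, the authors plan to report "associations of compliance with demographic, clinical, and other time-varying variables". No test or model is named there.
- **Use of the results.** The Results section says that "findings will inform the development of an intervention to address diabetes self-management and decision-making in adolescents with T1D". The Introduction gives the overall purpose as finding targets and strategies for later interventions.

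The sample size of 30 to 40 (Recruitment and Sampling) rests on how much qualitative data is needed, not on a power calculation.

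**The concern.** Three statements sit together: a goal in causal language (factors that influence glucose), a single per-test threshold, and permission to add tests after seeing the data. Read as written, any factor with p<.05 may be called a risk factor, however many were tried. With many factors and few people, some will cross that line by chance. Frequent sensor readings do not remove this problem for factors that vary only between people, because they add no people.

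What is at stake is the study's own product. A chance association reported as a risk factor could enter the grounded theory through the integration step, and from there the choice of intervention target. The concern is with wording and a decision rule that the article does state. That the factor list is absent is not the point, since it may stand in an analysis plan that is not shown.

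**Working it through.** **The plan's own figure.** The only error rate stated is 5% per test. For one test, 1 − (1 − 0.05)^1 = 0.05, which agrees trivially. The article gives no family-wise rate, number of tests or power to reproduce.

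**Inputs**

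- Per-test level: 0.05 (Quantitative Analysis).
- Sidedness: not stated for the mixed model. The phrase "1-tailed *t* tests will be used" concerns the baseline comparison of HbA1c groups. I assume two-sided tests.
- Number of factors, k: **not given, so assumed.** The Baseline Survey section says "The survey includes measures of diabetes self-management behaviors, depression, diabetes distress, attitudes towards diabetes technology, problem-solving, and self-efficacy with diabetes self-management", which is six constructs; Table 1 names eight instruments for them. Under Demographics and Clinical Characteristics, "Demographic measures include age, race and ethnicity, gender, and student and/or employment status" gives four variables. That section adds four clinical items and about four or five on device use, so about 12 or 13 in all. Hence k = 8 (instruments only) up to k = 8 + 12 = 20, or 21 with the fuller device count.
- Correlation between test statistics, ρ: not given. Range shown: 0 to 0.8.
- All nulls are taken as true.

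**Independent tests.** P(at least one false positive) = 1 − (1 − 0.05)^k

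- k = 8: 1 − 0.95^8 = 0.337
- k = 13: 1 − 0.95^13 = 0.487
- k = 14: 1 − 0.95^14 = 0.512
- k = 20: 1 − 0.95^20 = 0.642

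**Equally correlated tests.** With z = 1.96, φ and Φ the standard normal density and distribution function, and u the shared component, P = 1 − ∫ φ(u) [Φ((z − √ρ·u)/√(1−ρ)) − Φ((−z − √ρ·u)/√(1−ρ))]^k du, integrated numerically.

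| k | ρ = 0 | ρ = 0.5 | ρ = 0.8 | Expected false positives (0.05k) |
|---|---|---|---|---|
| 8 | 34% | 25% | 16% | 0.4 |
| 20 | 64% | 42% | 22% | 1.0 |

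**Check at the planned sample size.** A null simulation of one-at-a-time person-level correlation tests (n = 30, 35 and 40; 4,000 runs each) gave 25–26% for 8 factors and 43–44% for 21 factors at ρ = 0.5. The rate barely moved with n. This stands in for the mixed model, whose specification the article does not give.

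**Reading.** The lowest value in the table, 16%, is about three times the stated 5% (0.157/0.05 = 3.1). The chance passes one half only with 14 or more independent factors; at ρ = 0.5 it stays below one half even with 21.

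**The case against.** The strongest reply is that the quantitative part is a supporting one. The primary outcomes are qualitative, the sample was sized for qualitative sufficiency, and the Quantitative Analysis section says the measures serve to describe the sample and deepen understanding of each participant. The Mixed Methods Integration section adds that merged results, concordant or not, can raise hypotheses for later work. Factor lists and multiplicity rules commonly belong to an analysis plan. Nothing says that p<.05 alone selects an intervention target.

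Much of this stands. It means that strict family-wise control is not required and that the missing factor list is no fault. It does not rescue the sentence itself: the hypothesis-generating remark is about merged findings, while the mixed-model sentence sets out to find factors that influence glucose and the same paragraph gives a threshold for doing so. If the model is only supportive, that is where to say it.

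Three stronger readings are tempting and are not supported:

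- *A false risk factor is likely.* A reader might infer this from the number of variables collected. The article does not say that all of them enter the model, and likely, in the sense of better than even, needs about 14 or more nearly independent factors. The figures also assume that every null is true, whereas the Results section expects several real differences between the HbA1c groups.
- *The compliance associations are a second risk-factor screen, to be added to the first.* They are a planned report under a checklist and come under the 5% rule only through its general wording. A chance finding there bears on feasibility, not on glucose, so a combined count of tests would mix unrelated claims.
- *A formal multiplicity correction is mandatory.* For analyses labelled exploratory it is a choice.

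**Conclusion.** The point holds as a matter of wording and decision rule. The article presents an unranked search for glucose risk factors with an uncorrected 5% per test as its only criterion. If 8 person-level factors were tested, the chance of at least one false risk factor would be about 16% to 34%; with 20, about 22% to 64%.

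These figures assume two-sided tests, all nulls true, correlations from 0.8 down to 0, and a factor count that I inferred from the variables collected. They show that the error is well above 5% over that range. They do not estimate what this study will find. The compliance associations share the problem only secondarily.

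**What to change.** In the Quantitative Analysis section:

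1. Replace the stated aim of the mixed models with *explore associations with blood glucose levels*.
2. State that the mixed-model risk-factor analyses and any additional tests prompted by the data are exploratory and hypothesis-generating. Secondarily, say the same of the compliance associations.
3. Report every factor examined, whether or not significant, with its estimate and 95% confidence interval.
4. State that no factor will be named a risk factor or an intervention target on p<.05 alone.

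False-discovery-rate control within the glucose analysis is an optional addition.

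The cost is a few sentences and fuller reporting, with no new data or participants. The downside is more cautious language and fewer factors called significant.
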